#### General principles for analysis

All analyses will be conducted on an intention-to-treat basis, regardless of whether the infant is known to have received a full dose or not (for example, if the infants spit up all or some of the dose). All analyses will be performed with both person time (infant years of follow up) (primary analysis) and live births as the denominator. Random effects models and robust standard errors will be used to account for clustering of deaths with multiple births.

Separate analysis workshops will take place at the end of follow up in each of the three study sites. Data cleaning for the analysis of all the primary and secondary outcomes will be completed before the workshops and the databases will be locked. The randomization code will be provided to the members of the trial teams during the workshop. The code will first be provided as dummy variables (e.g. × and Y). After all analyses are completed the code will be provided as allocation groups (vitamin A and placebo). Analysis will be performed separately by site.

Individual site results will be presented to the DSMB at a joint meeting within 3 months of analysis in each site.

#### Flow of participants

The flow of the number of participants through assessment of eligibility, randomization, follow-up and analysis will be documented (Figure 2). Reasons for exclusions and withdrawals will be described.

**Figure 2 F2:**
[figure not shown]
**Structure of the study flow chart**.

#### Comparability of participants in intervention and control groups

Summary values (means, proportions) for several background characteristics in the intervention and control groups will include maternal age, parity, maternal education, wealth index of the household, place of delivery, singleton or multiple birth, sex of infant, birth weight, median age at supplementation and immunization status (time of first DTP immunization). No significance tests will be performed [28].

#### Main effects

For the primary outcome, all-cause mortality between supplementation and 180 days of age, data will first be analysed using person time, i.e. infant years of follow up, as the denominator. Hazard ratios and 95% confidence intervals comparing the effect of vitamin A on deaths in the first half of infancy between vitamin A and placebo groups will be calculated using Cox regression. In the unlikely event that there is imbalance between the treatment and control groups, the final statistical models will include adjustment for all imbalanced variables. The effect of vitamin A supplementation on all-cause mortality between supplementation and 180 days of age will also be assessed using enrolled infants as the denominator. The principles outlined above will be followed, and logistic regression will be used to compare mortality in the vitamin A and placebo arms.

The effect of vitamin A supplementation on secondary outcomes (all-cause mortality from supplementation to 12 months, all-cause mortality from supplementation to end of the neonatal period, hospitalizations) will be assessed using similar methods to the primary analysis; both person time and enrolled infants will be used as denominators for all analyses.

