##### Screening and enrolment

After the birth of a live infant, parents are asked for consent to participate in the study. Those who give written informed consent are screened to determine if the infant meets the eligibility criteria. Those consenting and eligible are given a single dose of 50,000 IU of vitamin A or placebo. The number written on the blister pack of vitamin A or placebo becomes the infant's ID, and an identity card is issued.

Infants are randomized individually within the geographical strata according to a computer-generated random number list, arranged in blocks of 20, in which unique identification numbers corresponds to one of the two interventions. Each new infant is assigned the next available study number. Previous experience has demonstrated feasibility to conduct the individually randomized controlled trial in these study clinics and communities.

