### Analysis plan for the three studies

#### Definitions

The primary outcome of the study is defined as a death between supplementation and 180 days of life (6 months). Secondary mortality outcomes are defined as a death between supplementation and 28 days of life, and a death between supplementation and 365 days of life. Severe morbidity is defined as one or more hospitalizations due to any illness between supplementation and day 180 of life. A hospitalization is defined as an admission to hospital as an inpatient, as reported by the mother. Infants will only contribute one hospitalization episode to the analysis, regardless of how many times they were hospitalized in the first six months of life.

Potential adverse events are defined as specific events occurring within 3 days of supplementation. These events include all deaths within 3 days of supplementation; bulging fontanelle confirmed by the research team through a physical examination of the infant; or primary caregiver reports of fever, vomiting, diarrhoea, inability to suck or feed, or convulsions in the first 3 days post supplementation.

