#### Sub-group analyses

The sub-group analyses listed below were specified *a priori *in the trial protocol.

The effect of vitamin A supplementation on all-cause infant mortality from 6 to 12 months by:

- Birth weight (< 1.5 kg, 1.5-1.9 kg, 2.0-2.4 kg, ≥ 2.5 kg, and as a continuous variable)

- Sex (male or female)

- Risk of death before and after receipt of first dose of DTP vaccine. For this analysis, person-time for each infant will be divided into before and after receiving DTP vaccine.

- Economic group (richest to poorest wealth quintiles, using principal components analysis)

- Maternal large-dose vitamin A supplementation (received or not received)

Site-specific results will be presented for all subgroups. Statistical interactions will be assessed using likelihood ratios tests for unadjusted hazard ratios or Wald tests for adjusted hazard ratios. If significance tests yield a p value < 0.01 then site specific mortality rates and hazard ratios comparing mortality in the vitamin A supplementation and placebo group in each sub-group will also be reported.

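### The final model adjusts for whatever looks imbalanced, with no criterion and no limit to pre-dose variables, and the only candidate list includes time of first DTP, which is a follow-up event

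*Protocol article*

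**What the plan says.** Three sections of the protocol article's analysis plan bear on this point.

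- **Main effects.** The primary hazard ratio "will be calculated using Cox regression". Should the arms turn out imbalanced, which the article calls unlikely, "the final statistical models will include adjustment for all imbalanced variables". The logistic analysis follows the same principles, and the secondary outcomes use similar methods.
- **Comparability of participants in intervention and control groups.** Ten background characteristics will be summarised by arm. The list ends with "birth weight, median age at supplementation and immunization status (time of first DTP immunization). No significance tests will be performed".
- **Sub-group analyses.** For the DTP question, "person-time for each infant will be divided into before and after receiving DTP vaccine".

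The supplement is given on the day of birth or in the next two days (Study intervention preparation, masking and administration). Immunisation status is collected at the follow-up visits (Follow up during infancy, Ghana and India). General principles for analysis says that databases are locked first, that groups carry dummy codes while the analyses are run, and that true allocation is released only afterwards.

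**The concern.** The adjustment rule has two faults.

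First, it does not fix the primary model. Imbalance has no threshold, and significance tests are ruled out. Interim analyses by the DSMB sets a single final criterion (P < 0.047), but an undefined judgement made on the data decides whether an unadjusted or an adjusted model supplies that P value.

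Second, the rule covers all imbalanced variables, and one of the ten listed is not a baseline variable. First DTP comes after dosing. Treatment could affect its timing, and an infant must survive to vaccination to have a value at all. A difference between arms in DTP time could therefore be a consequence of treatment, and the rule would answer it by conditioning on it. At stake is the primary mortality estimate in three trials that are meant to inform global policy.

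**Working it through.** **1. What the plan's figures fix.** This point disputes no number in the plan. As background, the Sample size section's 40,200 for India can be reproduced. A control risk of 40 per 1000 (assumed, since that section gives no enrolment-to-6-month rate), a 15% reduction, 85% power, two-sided 5%, continuity correction and division by 0.9 give 40,229.

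**2. Inputs for the check.**
- From the documents: 40,200 × 0.9 = 36,180 infants followed; 180-day control risk 5% (under-six-month mortality, India Study setting); hazard ratio 0.85; final two-sided P < 0.047.
- Assumed, not in the documents: DTP given from day 42 with mean about day 70; 10% never vaccinated; 50% or 70% of 180-day deaths before day 28.

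Expected deaths: 18,090 × 0.05 × (1 + 0.85) ≈ 1,673. The simulated trials averaged about 1,675.

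**3. Simulated Cox models, 120 trials per row.** Effects are either constant (0.85 throughout) or wholly before day 28. In the second case the early hazard ratio is 1 − 0.15/0.5 = 0.70 or 1 − 0.15/0.7 = 0.786, and 1.0 afterwards.

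| Effect; share of deaths before day 28 | Deaths with a DTP time / all | Deaths lost | Unadjusted HR (power) | HR with DTP time (power) | HR with DTP received yes/no (power) |
|---|---|---|---|---|---|
| Constant; 50% | 536 / 1,674 | 68% | 0.852 (0.91) | 0.856 (0.41) | 0.858 (0.88) |
| Constant; 70% | 320 / 1,675 | 81% | 0.855 (0.91) | 0.854 (0.26) | 0.866 (0.84) |
| Early only; 50% | 583 / 1,679 | 65% | 0.847 (0.89) | 0.997 (0.07) | 0.855 (0.88) |
| Early only; 70% | 350 / 1,676 | 79% | 0.850 (0.91) | 0.999 (0.04) | 0.862 (0.86) |

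A none/early/late coding gave the same results as received yes/no. With no true effect (200 trials), rejection was 0.04-0.05 in every model.

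**4. Why DTP time does this.** Infants without a value drop out, so every death that remains occurred after vaccination. The model then estimates the effect after vaccination only. If the effect is constant, that estimate is still about 0.85 but rests on far fewer deaths. If the effect is early, it is about 1.00.

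**5. Hand check of the power loss.** Use SE ≈ 2/√deaths and power = Φ(|ln 0.85|/SE − 1.986), where |ln 0.85| = 0.1625.
- 1,674 deaths: SE 0.049, power 0.91.
- 536 deaths: SE 0.086, power 0.46.
- 320 deaths: SE 0.112, power 0.30.

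The simulated 0.41 and 0.26 agree with the last two within Monte Carlo error (about 0.04).

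**6. A second setting.** With a control risk of 40 per 1000 and hazard ratios of 0.75 before DTP and 1.0 after, about 445 of 1,340 deaths keep a DTP time (67% lost). The Cox hazard ratio goes from 0.85 to 0.99, and the SE from about 0.055 to 0.095.

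**7. True baseline variables.** The SE of a standardised difference is 2/√N, which is 0.010 for 40,200 and 0.011 for 32,000. The probability that it exceeds 0.05 in size is below 0.00001. Adjusting for a strong covariate (hazard ratio 3, prevalence 30%) that is imbalanced at p = 0.05 moves the treatment hazard ratio by only about 1%.

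**The case against.** The strongest reply is that the harm is a possible reading and not a stated plan. Main effects does not cite the list in the preceding section and does not name DTP, the list serves a descriptive table, and the subgroup section handles DTP properly. This is fair: the link is inferred from adjacency and from the absence of any other list. But the rule says all imbalanced variables, nothing in it excludes DTP, and the list itself calls DTP time a background characteristic.

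The trigger would also seldom fire. In the simulations, receipt of DTP differed between arms by at most about 0.7 percentage points and median age at DTP by about 0.2 days. Few people would call that imbalance, provided vitamin A does not itself alter vaccination. This stands and limits the likelihood of harm. A reader might instead count 5% tests over the ten listed characteristics and infer that adjustment is likely. The documents do not support that, because they rule out significance tests.

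A reader might also infer that any adjustment for DTP erases the effect. It does not. Categorical codings leave the hazard ratio at 0.855-0.866. In a separate logistic check with an effect only before DTP, the received coding gave 0.86-0.89 when 2-10% of infants were never vaccinated. It approached 1.00 only if every surviving infant was vaccinated.

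Nor do the documents support the reading that analysts choose the model knowing the allocation. Under the dummy codes they could respond to the size of a difference but could not steer towards or against vitamin A.

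Finally, a threshold for imbalance and a covariate list may stand in a statistical analysis plan that is not shown. Their absence here is not the complaint. The complaint is that the article states a rule, and the rule as worded admits a post-randomisation variable.

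**Conclusion.** The point holds in a limited form. The stated rule makes the final primary model depend on observed imbalance, without a criterion and without restriction to pre-dose variables, and the only candidate list contains a variable that exists only for infants who live to vaccination.

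The damage is conditional. DTP time must be judged imbalanced and must enter as an ordinary covariate. About 65-81% of primary-outcome deaths then drop out, and power falls from about 0.9 to 0.26-0.41 under a constant hazard ratio of 0.85. The estimate goes to about 1.00 only if the effect is all early. These figures rest on the assumed DTP ages, vaccination coverage and early-death share.

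The open-ended rule matters little for true baseline variables in trials of this size. The DTP item is the reason to act.

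**What to change.** 1. Remove time of first DTP from the background characteristics and from the adjustment candidates. Report it as a follow-up descriptor and use it in models only as a time-varying quantity, as the subgroup section already does.
2. Name one primary model in advance: either unadjusted, or with a fixed set of pre-dose covariates (for example birth weight, sex, multiple birth and age at dosing) used whatever the balance.
3. Limit any imbalance-driven adjustment to pre-dose variables and label it a sensitivity analysis.

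A secondary and optional improvement concerns Tanzania, where "Infants are randomized individually within the geographical strata according to a computer-generated random number list": the Cox model there could be stratified by those strata.

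The cost is a change of wording before the randomisation code is released. No new data are needed.

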##### Follow up during infancy

Each enrolled infant is allocated to a home visit worker (contiguous study areas are allocated to FWs in advance) for further follow up visits till 12 months of age. All infants are contacted when aged 1, 3, 6 and 12 months by the home visit worker to document vital status, hospitalization, immunization, and information on feeding practices. Verbal autopsies are conducted to ascertain causes of deaths reported. Whenever hospital records are available these are photocopied and attached to the form. A hospitalization is defined as either an inpatient admission (where an infant receives an inpatient slip with a registration number and is allotted a bed) or a stay of ≥ 6 hours duration in the hospital including the emergency services, diarrhoea management room or any paediatric wards of the institution.

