### Timelines

Enrolment of participants started between June and August 2010 in the three studies and is likely to be completed by September 2012. After enrolment is completed, follow up visits will continue to be conducted for a period of 6 months. This will ensure that all enrolled infants have a chance to complete their 6 month follow up. A proportion of enrolled infants will therefore have less than 12 months follow up.

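### The supplementary logistic analysis of 12-month mortality keeps all enrolled infants in the denominator, although follow-up closes before many of them can reach day 365

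*Protocol article*

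**What the plan says.** All references are to the protocol article.

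- **Definitions** sets the 12-month outcome as "a death between supplementation and 365 days of life".
- **General principles for analysis** asks for "both person time (infant years of follow up) (primary analysis) and live births as the denominator", so person time leads.
- **Main effects** uses Cox regression for person time. For the count denominator, "logistic regression will be used to compare mortality in the vitamin A and placebo arms". It extends similar methods to the secondary outcomes, 12-month mortality among them, and adds that "both person time and enrolled infants will be used as denominators for all analyses".
- **Timelines** gives the recruitment period: "Enrolment of participants started between June and August 2010 in the three studies and is likely to be completed by September 2012". Visits then go on for six months, and the section draws the consequence itself: "A proportion of enrolled infants will therefore have less than 12 months follow up".
- **Follow up during infancy** differs by site. For India, "All infants are contacted when aged 1, 3, 6 and 12 months". Tanzania has the same four contact ages. Ghana visits monthly to 12 months.

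**The concern.** A yes/no outcome at day 365 has no value for an infant whose follow-up is closed while alive at, say, eight months. Person time copes with this through censoring. A logistic model over all enrolled infants does not: such an infant is in the denominator and can enter only as a non-death. The article applies this denominator to every analysis and makes no exception for the one outcome whose window outlasts the follow-up of late enrollees.

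The deaths lost in this way all fall between six and 12 months. The Discussion says that 12-month mortality was added because earlier studies suggested a negative effect in the second half of infancy. The analysis therefore loses information in the period for which the outcome was added.

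**Working it through.** The article prints no figure for the share of infants without 12 months of follow-up, so there is none to reproduce. It is derived here.

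**Inputs**
- Enrolment duration T (Timelines): from about 24.1 months (31 August 2010 to 1 September 2012) to 28.0 months (1 June 2010 to 30 September 2012).
- Follow-up after the last enrolment: 6 months (Timelines).
- Enrolled: 40,200 in India, 32,000 at each other site (Sample size).
- India mortality: 50 per 1000 to six months and 60 per 1000 to 12 months (India, Study setting), hence 10 per 1000 between. These are rates per live birth, used here as if per enrolled infant. The Sample size section gives only one rate for India, about 50 per 1000 infant mortality, and so no split.
- Assumptions: uniform enrolment; deaths spread evenly over months 6 to 12.

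**Step 1: share closed out before day 365.** Infants are enrolled at 0 to 2 days of age, so the share is 6/T.
- 6/28.0 = 21.4%; 6/24.1 = 24.9%.
- India: about 8,610 to 10,010 infants. Other sites: about 6,860 to 7,970 each.
- Rate rising linearly from zero: 1 − (1 − 6/T)² = 38% to 44%.
- Rate falling linearly to zero: (6/T)² = 5% to 6%.

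**Step 2: understatement of the 12-month risk in India.**
- Observed up to close-out: these infants miss on average half of the 6-12 month window. 8,610 × 0.010 × 0.5 = 43 deaths and 10,010 × 0.010 × 0.5 = 50 deaths. Over 40,200 this is 1.1 to 1.2 per 1000, so 60 would be read as about 58.8 to 58.9 (about 2% relative).
- Nothing learned after the six-month visit: the whole window is missed. 8,610 × 0.010 = 86 deaths and 10,010 × 0.010 = 100 deaths, or 2.1 to 2.5 per 1000. This is the upper bound.

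**Step 3: other sites.** No six-month risk is printed for Ghana or Tanzania. If 20 per 1000 die between months 6 and 12 (assumed, for example 40 then 60, or 30 then 50), the half-window calculation gives 20 × 0.214 × 0.5 = 2.1 to 20 × 0.249 × 0.5 = 2.5 per 1000, about 69 to 80 deaths of 32,000.

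**Step 4: effect on the ratio between arms.** Let 23% be closed out with half the window missed, so late deaths carry weight 1 − 0.23 × 0.5 = 0.885.
- Constant risk ratio 0.85: it stays 0.85.
- Early 0.85, late 1.2, control risks 30 then 20 per 1000 (assumed). Full follow-up: (30 × 0.85 + 20 × 1.2)/50 = 0.990. As planned: (30 × 0.85 + 17.7 × 1.2)/47.7 = 0.980.
- The same effects with India's 50 then 10 per 1000: 0.908 becomes 0.903.

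**The case against.** The strongest reply is that the lead analysis is already right. Person time is marked as primary, Cox regression comes first, and the same approach is carried to 12-month mortality. The problem is confined to a supplementary analysis of one secondary outcome. Close-out follows the calendar and not the arm, so the ratio hardly moves, as Step 4 shows. The authors knew of the truncation, and the coding of incomplete follow-up may be in an analysis plan that is not shown. All of this stands as a limit on weight. It does not remove the point, because the article states a denominator rule that, followed literally, gives too low a 365-day risk.

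Four stronger readings are tempting and are not supported.

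- A reader might infer that the 10% lost to follow-up are also to be counted as survivors. That figure is a sample-size assumption, and no passage says how lost infants are coded.
- A reader might take every second-half death among late enrollees as missed. That requires that nothing is learned after the six-month visit. Ghana's monthly visits contradict it, and Tanzania's key informants weaken it. For India it is possible, since no contact between months 6 and 12 is described, but it remains an upper bound.
- A reader might infer that the trial would hide late harm. The shift is small. Moreover, any cumulative contrast from supplementation to 12 months is dominated by early deaths, and a censored Cox hazard ratio also gives the late period less weight. This is not peculiar to the logistic model.
- General principles for analysis names live births as the second denominator, where Main effects names enrolled infants. A reader might infer that infants never randomised enter the comparison. Given the intention-to-treat statement beside it, this is a wording mismatch only.

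**Conclusion.** The point holds for the enrolled-infants analysis of 12-month mortality. That denominator and the follow-up timeline cannot both stand without a rule for infants closed out before day 365. About 21-25% of infants are affected under uniform enrolment, and about 5-44% across linearly falling or rising enrolment; the September 2012 end date is itself a forecast. In India the absolute 12-month risk would be read low by about 1.1-1.2 per 1000, and by at most about 2.1-2.5. The main consequence is understated absolute risk. The ratio between arms changes little unless early and late effects differ, and then it is pulled towards the early effect. The primary Cox analysis and the 28-day and six-month outcomes are not affected by this close-out.

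**What to change.** 1. Keep Cox regression on person time as the lead 12-month analysis, with infants censored at the last date known alive.
2. Restrict the 12-month logistic analysis to infants enrolled at least 365 days before the site's close-out date. This selects on calendar date alone, so the randomised comparison is preserved. Alternatively, replace it with Kaplan-Meier 365-day risks per arm and their difference.
3. Use enrolled infants as the name of the second denominator in both General principles for analysis and Main effects.

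The cost is wording only, with no extra visits or data, and it can be done before the code is released. The restricted analysis would use about 75-79% of infants. For a 15% reduction from an assumed 12-month control risk of 60 per 1000 (two-sided 5%, 10% loss), keeping 77% lowers power from about 96% to 91% with 40,200 enrolled and from about 92% to 83% with 32,000. Those starting values assume 12 months of follow-up for all infants not lost, which the timeline does not provide. The Kaplan-Meier option uses every infant.
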